## SECTION A

### STUDY OUTLINE

#### **A.1 TITLE OF Study: The impact of a family planning support intervention on pregnancy desires and contraceptive use among recently postpartum HIV positive women delivering at MRRH**

#### **A.2 SUMMARY**

Explain why this study is being conducted, using lay terminology.

*Guidance note:*

*Please convey what you think is the importance of the research and WHY it is being carried out.*

HIV status and availability of ART have been found to widely influence the desirability and expectations to have children among childbearing women living with HIV (Nieves et al., 2015; Kaida et al., 2011). Up to 85% of the pregnancies within 3 years following ART are often unwanted, often leading to illegal abortions and maternal deaths (Desgrees-Du-Lou et al., 2002).

Uganda's HIV epidemic has declined over time to about a sero prevalence of 7.2% and this decline has been attributed in part to improved prevention behavior like condom use, reduction in multiple concurrent partnerships and other strategies to prevent unwanted pregnancies. Specifically, HIV prevalence is estimated at 7% among women attending antenatal clinics in Uganda (UN, 2010). Whereas ART availability has improved general health outcomes through viral load suppression and immune reconstitution, there is still a high unmet need for family planning among HIV positive women in Uganda (Snow et al., 2011), where modern contraceptive prevalence is at 33% in the general population despite the widespread promotional messages across the country. This continues to expose HIV positive women to increased risks of unwanted/unplanned pregnancies, perinatal HIV transmission, pregnancy complications, and increased economic burden of care for self and others among others.

The high average fertility rate of 5.9 children per woman in Uganda may further complicate the immunity and wellbeing of the already burdened HIV positive women and their families even amongst those already accessing HIV care (Muyindike et al., 2012; Homsy et al., 2009).

Supporting HIV positive women to delay or prevent an unwanted pregnancy may improve women's health through family planning choices, regular health reviews, and support. A cohort study that was done in Mbarara amongst HIV-infected women documented 50% of the enrolled women having no desire for a (another) child during the 4 years since ART initiation, 51% had a serodiscordant partner, with only 45% using effective contraceptive method. Key predictors of contraceptive use were family planning goals within the DYAD. One of the key predictors of effective contraceptive use was male partner involvement and CD4 count. The WHO recommends dual contraception (use of condoms and a hormonal or permanent method) to prevent both HIV transmission and unwanted pregnancies (WHO,2014).This prospective intervention study aims at providing information on whether continuous family planning accessibility and support has a measurable impact on pregnancy intentions and contraceptive usage among postpartum HIV positive mothers delivering at MRRH, SW Uganda.

### **A.3 OBJECTIVES**

List the major objectives/hypothesis, which have governed your choice of study design

#### **General objective**

To test the effect of a family planning availability and support intervention on pregnancy intentions and use of effective contraception among recently postpartum women living with HIV who delivered at MRRH.

#### **Specific objectives**

1. To assess the influence of the intervention on pregnancy intentions among recently postpartum HIV positive mothers delivering at MRRH, SW Uganda one year after the intervention.

[figure not shown]

2. To assess the influences of the intervention on contraceptive uptake among recently postpartum HIV positive mothers delivering at MRRH, SW Uganda
3. To identify factors that influence pregnancy intentions and contraceptive use
4. To assess the influence of the intervention on the incidence of unintended pregnancy among recently postpartum HIV positive mothers delivering at MRRH, SW Uganda
5. To assess the influence of the intervention on the well being of recently postpartum HIV positive mothers delivering at MRRH, SW Uganda
6. To explore decision making challenges and perceptions of family planning among HIV positive women.
7. To assess the role of sexual partners on pregnancy intentions and effective contraceptive use

#### **A.4 METHODOLOGY**

Outline how you intend to achieve the objectives of the study.

*Guidance notes:*

*For each objective/hypothesis:-*

- *define the target population*
- *describe how the sample(s) is(are) to be recruited from the target population(s)*

*Even if the main thrust of the research is biomedical, the rationale behind your use of social science methods (e.g. patient interviews) should be clear.*

*describe how the sample(s) is(are) to be recruited from the target population(s)*

[figure not shown]

This will be a prospective randomized controlled trial of 2 arms.

- I. We intend to enroll a total of 320 HIV positive women delivering at MRRH. These will be equally randomized into the intervention arm (Family planning support) and control group (no family planning support, except the routine counseling following discharge). These women will be followed for 1 year. Eligibility will also require access to a mobile phone.

Natural family planning methods like lactation amenorrhea, withdrawal methods and others have been presented with mixed literature, painting a grim picture on their effectiveness as standalone contraceptive methods especially among HIV positive women. All women are advised to exclusively breast feed for 6 months while on ART (MoH, 2015). Because hormonal contraception inclusive of estrogen interferes with breast milk production among lactating mothers, progestin-only methods will be recommended to the women.

#### **I. Randomization:**

Consecutive numbers ranging from 001 to 320 will be computer generated to indicate the 2 main groups into which mothers can be randomly assigned and enrolled. These consecutive numbers will be labeled on top of the opaque envelopes. To be eligible, mothers must be HIV positive, have had a delivery within the last 48 hours, above 18 years of age, anticipating to begin family planning post partum, have a spouse/sexual partner whom we may contact or invite to participate in the study, must be mentally stable and qualify for any family planning method available. Once eligibility of a mother is confirmed, they will be invited to participate in the study.

The aim of the study and details of the procedures to be involved in the trial, potential side effects and therapeutic benefits will be explained before randomization occurs. Once the mothers consent to participate in the study, a study number will be allocated by the nurse research assistant (**who will be recruited to work on the ward/post natal clinic for this study**) by taking the next in a series of similar opaque envelopes provided to conceal allocation of groups. These opaque envelopes will be labeled with computer-generated list of numbers with group allocation (either Intervention group or Control Group) of the mothers randomized in blocks of 20. Nurse research assistants will be blinded to the group allocation until eligibility and study participation is confirmed. They will also be blinded to hypothesis of the study.

A blood sample will be drawn at baseline to confirm the HIV status and or do a CD4 cell count in case it is unknown at the time of enrollment. This will be done to support women enroll for the recommended Option B+ incase the women are not yet lifelong ART].

A different study nurse will be enrolled and trained to specifically collect data from participants. The socio-demographic data and obstetric characteristics will be documented. Other documented potential covariates of contraceptive use like participant age, primary partner's age, primary partner's HIV status, personal and partner fertility desires, number of children, most recent CD4 cell count, Efavirenz-containing ART Regimen (due to its association in decreasing levels of hormonal contraception thus recommending dual methods and its teratogenicity concerns-although these concerns have been found to be exaggerated), socio-economic status, body mass index, education level, time on ART . Prior contraceptive use experiences, fertility desire/ pregnancy intentions or aspiration will be measured using the CDC pregnancy Risk Assessment Monitoring System Instrument (Ahluwalia et al., 1999)

Effective contraception use will be defined as consistent use [both self report and observational chart review from study nurse at the family planning clinic] of a family planning method (including consistent condom use) , including dual contraception (use of condoms and another contraceptive method-hormonal or permanent) for HIV-sero discordant couples/partners (for participants who know partner's status). A primary partner will be defined either as a regular spouse, who is also a regular sexual partner or the most recent sexual partner if no main partner is named. These sexual partners will also be enrolled and interviewed at baseline and at 1 year. In case a consented mother ends up with a serious adverse event, the time and indication will be documented and reported. In case a woman changes the contraceptive method, the reasons for the change will also be documented.

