## A.8 QUALITY ASSURANCE

A.8.1 What procedures are in place to ensure the quality of the data?

*Guidance notes:*

*For qualitative data (for example) what procedures will be used to check translations or compare data obtained from different sources?*

*For quantitative data (for example) how will transcription errors be minimised?*

*Give some detail on how methods are going to be piloted, if appropriate*

- An instrument to collect the required data has been adapted from the tools used by other researchers in other sites.
- Computer-generated numbers will be used to randomize mothers into this study. These numbers will be in opaque envelopes to blind the observers on the group to which the next mother will be randomized and observed. The Investigator or researchers/ observers will not have prior knowledge of the treatment allocated to the next patient to avoid bias into the random allocation process.
- Details of the aim and procedures to be involved in the trial for the three groups, potential side effects and therapeutic benefits will be explained to the eligible patients on admission by the nurse research assistant before randomization occurs. Once the mothers consent to participate in the study, opaque envelopes containing computer-generated consecutive numbers from 001-320 will then be opened by the researcher and the random group allocation of the mothers will be communicated.
- Improved routines at the time of discharge will be observed for all mothers on the ward regardless of the study intervention. Family planning counseling and advice will be availed to all mothers at discharge.
- Routine reviews, counseling and support will be done to ensure adequate management of side effects and other family planning concerns that may arise during the course of the study.
- Internationally recognized brands of contraceptives or their equivalent from national Medical stores (NMS) will be used for this study
-

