- Two Nurse research assistants will be **recruited** and **trained** as observers and data collectors to increase accuracy and consistency in documenting the needed data. They will be assisted by the post natal clinic staff and these research assistants will be blinded to the hypotheses of this study. To minimize observer bias and facilitate participant randomization, one nurse research assistant will deal with enrollment, family planning counseling and support while another will entirely follow up participants and collect the required data at different time points. Senior Obstetricians will supervise the trial and administration of contraceptives on post natal clinic.
- Mothers will be free to withdraw from one family planning method to another following their doctors advice.

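### The protocol contradicts itself on whether the arm is marked on the outside of the envelope and on who handles it, and it fixes the block size at 20

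*Protocol*

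**What the plan says.** Protocol section A.4, under Randomization, describes the envelope twice. The opening lines say: "These consecutive numbers will be labeled on top of the opaque envelopes". The next paragraph says: "These opaque envelopes will be labeled with computer-generated list of numbers with group allocation (either Intervention group or Control Group"), and continues "of the mothers randomized in blocks of 20".

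The same section states its aim and the order of events. After consent, the nurse research assistant allocates a study number "by taking the next in a series of similar opaque envelopes provided to conceal allocation of groups". It adds: "Nurse research assistants will be blinded to the group allocation until eligibility and study participation is confirmed".

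Section A.8 (Quality assurance) says that after consent "opaque envelopes containing computer-generated consecutive numbers from 001-320 will then be opened by the researcher", and that the woman's group is then communicated. It also says that the researchers will not know the next allocation in advance. On staffing it says that "one nurse research assistant will deal with enrollment, family planning counseling and support", while a second nurse follows women up and collects the data.

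The ratio is 1:1 (A.4: "These will be equally randomized into the intervention arm (Family planning support) and control group") with 320 women planned.

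**The concern.** Whoever prepares the envelopes has to know what goes on the outside and what goes inside. A.4 uses the same verb, labelling, for the number on top and for the group. If the second sentence is carried out as written, the arm is visible before a woman has been judged eligible and has consented.

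Foreknowledge would matter here because some eligibility criteria call for judgement: that the woman expects to start family planning, and that she is mentally stable. The first bears directly on the first primary outcome, effective contraceptive use at 12 months. There is also room to pass a woman over. The hospital figures under A.5.3 (more than 12,000 deliveries a year, 13% HIV prevalence) imply at least 12,000 × 0.13 = 1,560 deliveries a year to HIV-positive women, before other criteria, for 320 places. An intention-to-treat analysis does not undo selection that took place at entry.

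The fixed block raises a second, smaller question. Only one arm receives vouchers and reminders, so staff who support the women can learn past allocations. One nurse both enrols and supports.

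**Working it through.** **Step 1. The statements side by side.**

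- Outside of the envelope: A.4 says number only, then number with group.
- Inside of the envelope: A.8 places the numbers inside and has the group communicated once the envelope is opened, which implies that the allocation is inside too.
- Handling: in A.4 the nurse research assistant takes the next envelope; in A.8 a researcher opens it. Neither section says whether these are the same person.
- Aim: both sections state concealment before assignment.

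The sentence that puts the group on the label is the one that does not fit.

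**Step 2. Predictability from a fixed block of 20.** The protocol gives no figure for this. Inputs from the protocol: 320 women, 1:1 allocation, blocks of 20, hence 320/20 = 16 complete blocks with m = 10 places per arm in each. Assumptions that the protocol does not state: balance within each block, and an enrolling nurse who knows every earlier allocation and the block size.

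*Assignments certain before opening.* Let D(a, c) be the expected number of certain assignments left when a and c places remain in the two arms. If a = 0 or c = 0, D = a + c. Otherwise D(a, c) = [a·D(a−1, c) + c·D(a, c−1)]/(a + c). From m places each, this gives 2m/(m + 1):

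- per block: 20/11 = 1.82
- share: 1.82/20 = 9.1%
- whole trial: 16 × 20/11 = 29.1 of 320

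*Correct guesses when always naming the arm with more places left.* G(a, c) = max(a, c)/(a + c) + [a·G(a−1, c) + c·G(a, c−1)]/(a + c), with G(0, 0) = 0. From 10 and 10 this gives 12.34. The closed form agrees: m + ½[2^(2m)/C(2m, m) − 1] = 10 + ½[1,048,576/184,756 − 1] = 10 + ½(5.676 − 1) = 12.34.

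- share: 12.34/20 = 61.7%, against 50% by chance
- whole trial: 16 × 12.338 = 197 of 320, against 160 by chance

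**Step 3. How these depend on the assumptions.** The certainty figure needs the block size. The guessing figure needs only a complete tally: finished blocks balance, so the arm that is behind overall is the arm with more places left in the current block.

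The same recursion for other fixed sizes:

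| Block size | Certain | Best guess correct |
|---|---|---|
| 4 | 33% | 71% |
| 10 | 17% | 65% |
| 20 | 9% | 62% |

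Twenty is therefore less predictable than the smaller fixed sizes.

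**The case against.** The strongest reply is that the protocol says repeatedly that allocation is concealed. The envelopes exist for that purpose, the nurse is blinded until participation is confirmed, consent comes before the envelope is taken, and A.8 rules out knowledge of the next allocation. Opaque envelopes that have to be opened would serve no purpose if the arm were printed on them. The label sentence may only mean a computer list that pairs each number with a group. This stands. It makes the sentence a drafting fault, but does not remove the fault, because the sentence is the instruction that someone preparing envelopes would follow.

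Several stronger readings are tempting and are not supported:

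- **That all 320 allocations are visible in advance.** This is a worst case resting on one ambiguous clause that the rest of the text contradicts.
- **That the nurse who enrols and counsels opens the envelope.** A.4 has a nurse research assistant take it and A.8 has a researcher open it. That they are the same person is an inference.
- **That the A.8 envelopes contain numbers and nothing else.** A.8 does not say so, and its next words imply that the group is inside.

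On the block, it is fair to say that a fixed 20 is not an error, that nothing shows the nurse is told the size, and that the research assistants are to be blinded to the hypothesis, which weakens any motive to steer. The protection is limited, since the same staff explain the study's aim to mothers. That the protocol never mentions sealing is silence on an operational detail and is not counted here as a fault.

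**Conclusion.** The point holds as an inconsistency in a procedure that the protocol itself sets. One sentence of A.4, if followed literally, would reveal the arm before consent, against the other sentence in A.4 and the concealment stated in A.4 and A.8. The two sections also leave open who opens the envelope. Neither amounts to evidence that concealment will fail, and no size of bias in the primary outcomes can be derived from the documents.

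The fixed block is a secondary weakness. At most about 29 of 320 assignments (9%) would be certain, and best guessing would be right about 62% of the time. Both figures are upper limits for envelopes that hide the arm: they assume a perfect tally of past allocations, and the first also assumes knowledge of the block size. The protocol states neither. The correction is worth making because it costs almost nothing before enrolment, and selection at entry cannot be repaired afterwards.

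**What to change.** - Reword A.4 so that only the sequence number is on the outside and the allocation card is inside a sealed opaque envelope.
- Require the woman's study ID and the date to be written on the envelope before it is opened, so that each envelope is committed to one woman.
- Replace the fixed block of 20 by randomly varying block sizes that are not disclosed to enrolling staff. This removes certainty about where a block ends. It does not remove the advantage of keeping a tally, which grows as blocks get smaller, so the sizes should not all be small.
- Reconcile A.4 and A.8 on what the envelope contains and on who takes it and who opens it.

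The cost is rewording and regenerating the list before enrolment starts; no extra women are needed. Sixteen complete blocks of 20 guarantee 160 per arm. With varying sizes, an incomplete final block may leave a slight imbalance, at most half the size of that block.

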#### A.5 PARTICIPANTS

Please provide the following information on the participants with/from whom you expect to be collecting data:

##### A.5.1 Age / Sex: (please enter the expected number in each of the boxes)

|        | Neonates
(<28 days) | Infants
(1-11 months) | Young children
(1-9 years) | Adolescents
(10-17 years) | Adults
(18 yrs & above) |
|--------|------------------------|--------------------------|-------------------------------|------------------------------|----------------------------|
| Males  |                        |                          |                               |                              | Up to 160                  |
| Female |                        |                          |                               |                              | 320                        |

*Guidance notes:-*

*This age/sex breakdown helps convey how vulnerable the participants will be*

*If you are unable to give precise figures, state estimates and give an explanatory sentence in the space below*

[figure not shown]

A.5.2 What specific measures are in place to take into account women of childbearing age?

*Guidance notes:*

*women may have different responses to disease processes*

*The developing foetus may be particularly vulnerable in intervention trials*

The study involves administration of accredited contraceptive (hormonal or IUD) 6 weeks after the delivery of the baby. The contraceptives are not known to circulate into the lactating milk. These are; condoms, injectables, contraceptive pills, IUDs and implants. However, estrogen-containing contraceptives have been found to decrease milk production and therefore progesterone only methods or non-hormonal methods are recommended for lactating mothers.

A.5.3 Describe how and where the participants are to be recruited?

*Guidance notes:*

*This is distinct from the statistical sampling method described in A.4. You should outline the procedures for recruitment of each group of participants, include details on:*

- *the setting (e.g. Country, Town, District, on the ward, out-patient department, in the home)*
- *inclusion and exclusion criteria for selection, if relevant (e.g. "Women of child-bearing age will be excluded")*

To be eligible, mothers must be HIV positive, have had a delivery within the last 48 hours, above 18 years of age, anticipating to begin family planning post partum, have a spouse/sexual partner, must be mentally stable and qualify for any family planning methods available.

The Randomized Controlled Trial (RCT) study will purposively be carried out in the Maternity ward of Mbarara Regional Referral Hospital (MRRH), south western Uganda which also doubles as a Mbarara University Teaching Hospital for the faculty of medicine. The hospital is located in Kamukuzi Division, Mbarara Municipality along 30° 20'E and 31° 20'E longitude and 1° 30'S and 0° 30'N Latitude (DISH, 2011 <http://www.ugandadish.org/>). The regional referral hospital receives mothers from different tribal and socio-demographic locations in Uganda. The hospital is equipped with trained staff, midwives, and obstetricians able to offer comprehensive family planning facilities. The Hospital also have a good theatre/mini theatres for additional therapeutic/ surgical procedures that may be required for these post partum mothers. Mothers received in this hospital may also represent different mothers from various social and demographic backgrounds. MRRH records document > 12,000 deliveries annually and a 13% HIV prevalence for women delivering at the maternity ward of MRRH.

*A.5.4 Please justify your choice of sample size (as described in A.4)*

Pregnancy desires tend to be lower among HIV positive women (Kaida et al., 2015). Post partum pregnancy desires also tend to be low amongst women. Additionally, the “serious problem” highlighted by one third of the HIV positive pregnant women in a Ugandan study reflected an unmet need for contraception services, family planning support and unclear conjugal fertility aspirations (Snow et al., 2013).

In a superiority trial, one’s null hypothesis is that the two groups are equal and alternative hypothesis (or your main hypothesis) would be that one intervention is better (superior) than the other, in this case family planning support and availability. Two primary outcomes have therefore been suggested for this study; 1) Confirmed consistent use of an effective contraceptive method at 12 months and 2), pregnancy desire/aspirations among the HIV positive women. According to Nieves et al (2015), the rate of effective contraceptive use was found to be 45% amongst HIV positive women accessing HIV care at MRRH, although most of the contraceptive use was driven by condom use. Other studies have revealed that contraceptive prevalence would be 16 to 23 percent greater if all women lived in a cluster with the highest quality of care compared with the lowest one (Mensch et al., 1996). Another study also documented that the provision of the family planning voucher had a significant impact on contraceptive experimentation and long-term contraceptive use by an increase of 18 percentage points (Ashraf et al., 2014). We therefore hypothesize that improved family planning support and voucher will increase in effective contraceptive use among HIV positive postpartum women to at least 63%. This will therefore require a total of 156 women per group and an overall total of 312 HIV positive post partum women to have a 90% chance of detecting a significant increase at the 5% level.

For the second primary outcome, Nieves et al (2015) documents a pregnancy desire/aspiration rate of 33% for any HIV positive sexually active women attending ART clinic. Specifically, Snow et al (2014) also reported a lower and significant likelihood in desiring more children in future of 27.7% among married or cohabiting HIV-positive women when compared to 56.4% among HIV-negative women. Improved family planning accessibility and support offered through a voucher reduced the rate of births in the next year following the intervention to 6.8% (Ashraf et al., 2012). We therefore hypothesize a decrease in pregnancy or births in the next one year following our intervention to 6.8% with improved family planning availability and support among the recent post partum HIV-positive women. We shall therefore require a total of 80 women in each of the two groups and a total of 160 women in total to have a 95% chance of detecting a significant increase in pregnancy aspirations at the 5% level.

[figure not shown]

The participant enrolment and analyses will be done consecutively for the two primary outcomes. Up to 160 spouses/sexual partners will also be required to match their spouses in the intervention group. Initiation of a modern family planning method at any facility of choice, rate of pregnancy, time period of family planning discontinuation and or change will also be documented.

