### 3.4.2 Data Analysis Plan

Data analysis will be by intention-to-treat (ITT) consisting of all mothers randomized and thus supposed to be treated (Lesaffre, 2008). Descriptive statistics will be used to describe key characteristics of study participants. Different variables will be explored for normal distribution. Selected demographic, clinical, post-natal factors will be compared for differences and similarities in the groups. We will compare dichotomous outcomes between study groups by estimating crude odds ratios with 95% confidence intervals, and testing for differences between groups with chi-squared testing and a level of significance of 0.05. Continuous outcomes will be compared using t-tests. A Mantel-Haenszel test will also be done to control for different variables. Crude relative risks will also be derived. Relative risks with 95% confidence Interval (two tailed) will be calculated and used to compare contraception effectiveness and pregnancy intentions in all groups. Factors associated with effective contraception use and pregnancy intentions will be explored using univariate analysis and for results whose p value  $\leq 0.10$ , a multivariate analysis will be done to rule out confounding factors.

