### 3.4.3 Data Reporting

The means will be presented with their standard deviations. Relative risks and odds ratios will be presented with their 95% confidence Intervals. Two-tailed statistical analysis will be used and statistical significance will be defined at level of  $p < 0.05$ .

[figure not shown]

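### Two primary outcomes are each tested at the full two-sided 5% level with no rule linking them; if either may be claimed as success, the chance of a false positive is up to about 10%

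*Protocol*

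**What the plan says.** Section A.5.4 (justification of sample size) announces the structure: "Two primary outcomes have therefore been suggested for this study". The first is "Confirmed consistent use of an effective contraceptive method at 12 months"; the second is "pregnancy desire/aspirations among the HIV positive women".

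Each outcome has its own sample size calculation:

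- Contraceptive use, 45% against 63%: 156 women per group, 312 in all, "to have a 90% chance of detecting a significant increase at the 5% level".
- Pregnancy desire, with 33% and 27.7% cited as background rates and 6.8% as the target: 80 per group, 160 in all, "to have a 95% chance of detecting a significant increase in pregnancy aspirations at the 5% level".

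Section 3.4.2 compares dichotomous outcomes by "testing for differences between groups with chi-squared testing and a level of significance of 0.05". Section 3.4.3 adds: "Two-tailed statistical analysis will be used and statistical significance will be defined at level of" p below 0.05.

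Only one sentence, at the end of A.5.4, links the two outcomes: "The participant enrolment and analyses will be done consecutively for the two primary outcomes". It does not say which outcome comes first, or that the second test depends on the result of the first.

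**The concern.** With two primary outcomes, each tested at 5%, the error rate of the trial as a whole depends on what counts as success. If both must be significant, there is no inflation. If the second is tested only after the first succeeds, there is none either. If a significant result on either is enough, the chance of at least one false positive rises above 5%.

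The protocol spends the full 5% twice and does not say which of these applies. The trial could therefore miss on contraceptive use, reach p<0.05 on stated pregnancy desire, and be reported as positive on a primary outcome, with nothing in the protocol to prevent it. A rule chosen after the results are known would not be credible.

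**Working it through.** **Inputs from the protocol.** Two primary outcomes; two-sided 0.05 for each; 45% against 63% with 90% power; 27.7% or 33% against 6.8% with 95% power (all A.5.4, with sidedness from 3.4.3); 320 women randomized equally, so 160 per arm (A.4). The protocol gives no correlation between the two tests, so the correlations below are assumptions.

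**Step 1: does each stated sample size use the full 5%?** With unpooled variance, n per group = (z₁₋α/₂ + z₁₋β)² × [p₁(1−p₁) + p₂(1−p₂)] / (p₁−p₂)².

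- Contraceptive use: (1.960 + 1.282)² = 10.507; 0.45×0.55 + 0.63×0.37 = 0.4806; 0.18² = 0.0324. So n = 10.507 × 0.4806 / 0.0324 = 155.9, that is 156, which matches the protocol exactly. The pooled-variance version gives 160.
- Pregnancy desire from 27.7%: (1.960 + 1.645)² = 12.995; 0.277×0.723 + 0.068×0.932 = 0.2636; 0.209² = 0.0437. So n = 78.4, that is 79 (82 pooled), against the stated 80. Starting from 33% gives only 54 (58 pooled), so 27.7% appears to be the rate used.

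Both sizes therefore rest on a full two-sided 5%.

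**Step 2: chance of at least one false positive if the intervention affects neither outcome and either may be claimed.** For independent tests this is 1 − 0.95² = 0.0975. It can never exceed 0.05 + 0.05 = 0.10. For correlated tests, a bivariate normal calculation of 1 − P(|Z₁|<1.96, |Z₂|<1.96) gives:

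| Assumed correlation | Chance of at least one false positive |
|---|---|
| 0 | 9.75% |
| 0.2 | 9.6% |
| 0.5 | 9.1% |
| 0.7 | 8.3% |
| 0.9 | 7.0% |

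**Step 3: what control would cost at 160 per arm, all analysed.** Power = Φ{[|p₁−p₂|√n − z₁₋α/₂√(2p̄(1−p̄))] / √[p₁(1−p₁)+p₂(1−p₂)]}. For contraceptive use at 0.05 this is Φ[(2.277 − 1.960×0.705)/0.693] = Φ(1.29) = 90.2%.

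| Two-sided level | Contraceptive use, 45% vs 63% | Pregnancy desire, 27.7% vs 6.8% |
|---|---|---|
| 0.05 | 90.2% | 99.9% |
| 0.04 | 88.4% | 99.9% |
| 0.025 | 84.3% | 99.8% |
| 0.01 | 74.7% | 99.3% |

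- Fixed sequence: contraceptive use keeps 0.05 and 90.2%. Pregnancy desire can be confirmed only if both tests succeed. On these rates the chance of that is at least 0.902 + 0.999 − 1 = 0.901, against 99.9% ungated.
- Equal split, 0.025 each: 84.3% for contraceptive use, about six points lower. Restoring 90% would take 189 per group (378 in all) with pooled variance, or 185 (370) unpooled.
- Unequal split, 0.04 and 0.01: 88.4% and 99.3%, with total error at most 0.04 + 0.01 = 0.05.

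**The case against.** The strongest reply is that part of this is silence. The protocol nowhere says that either outcome alone makes the trial positive, and success rules are often left to a statistical analysis plan, which is not at hand. That stands in part: the inflation is conditional on an either-outcome reading. But the protocol does not merely leave the matter open. It fixes the full 5% for each outcome in its sample sizes and its test rule, and an alpha split written later would contradict both and lower the stated power for contraceptive use.

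Two stronger readings are tempting and are not supported:

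- A reader might infer that the true error is about double the rate the protocol promises. The protocol states 5% for each outcome and never states a rate for the trial as a whole. The figure near 10% is the independence case, it applies only when neither outcome is affected, and both outcomes are measured in the same women, so the rate may be lower.
- A reader might infer from the word *consecutively*, with needs of 160 and 312 women, that one outcome will be analysed while enrolment for the other continues. Section A.4 describes one enrolment of 320 women followed for a year, 3.4.2 requires intention-to-treat on all mothers randomized, and specific objective 1 assesses intentions one year after the intervention. The sentence may mean only that women are enrolled consecutively and one analysis follows the other. It needs clarifying; it does not show staggered analyses.

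It can also be objected that any testing order is a choice. A.5.4 lists contraceptive use first, but the title, the general objective and specific objective 1 put pregnancy desires or intentions first. That is fair, and the choice belongs to the sponsor.

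**Conclusion.** The point holds in a conditional form, as something that should be fixed. The protocol commits a full two-sided 5% to each of two primary outcomes and contains no split, gate or requirement that both succeed. If either alone may be claimed, the chance of at least one false positive is up to about 10% when neither outcome is affected: 9.75% if independent, 9.1% at correlation 0.5, 8.3% at 0.7, with the correlations assumed. If both were required, there would be no inflation, but the protocol does not say so. Neither stated sample size is arithmetically wrong because of this.

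**What to change.** Replace the sentence in A.5.4 on consecutive enrolment and analyses. The default is a fixed sequence in the order A.5.4 lists the outcomes, for example:

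> Effective contraceptive use at 12 months is tested first at two-sided 0.05. Pregnancy desire is tested at two-sided 0.05 as a confirmatory outcome only if the first test is significant; otherwise its result is descriptive. Both outcomes are analysed once, after all 320 women have completed 12-month follow-up.

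This needs no extra women and keeps about 90% power for contraceptive use. The cost is that pregnancy desire, which is specific objective 1, becomes descriptive if contraceptive use is not significant.

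If the sponsor does not want desire gated, an unequal split such as 0.04 for contraceptive use and 0.01 for desire holds the total at 5%. The power statement for contraceptive use should then be lowered to about 88%, and the 0.05 threshold in 3.4.2 and 3.4.3 amended for the two primary outcomes. Requiring both outcomes to succeed would also control the error, if that is what is meant.

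Under any of these rules the second outcome needs one definition first: A.5.4 names pregnancy desire but takes its 6.8% target from pregnancies or births. The power figures quoted for desire depend on that target. The rule should be fixed before any outcome data are compared by arm.
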